### Genetic dysregulation of Endothelin-1 and microvascular angina

1.3

The PRIZE trial is notable amongst cardiovascular clinical trials for defining eligibility by genetic analysis thus invoking a ‘precision medicine’ pathway whereby therapy will be targeted at those most likely to benefit. The genetic variant tested during screening for the PRIZE trial is the G allele of the rs9349379 SNP (single nucleotide polymorphism) found in the third intron of the PHACTR1 gene on chromosome 6. This variant has been linked to cardiovascular risk via enhanced Endothelin (EDN1) gene expression and is relatively common, with an estimated population frequency of 36% [23], [24]. In a sub-study of the British Heart Foundation Coronary Microvascular Angina (CorMicA) trial, patients with the rs9349379-G allele had significantly increased circulating concentrations of ET-1 as well as a higher likelihood of CMD, more myocardial perfusion defects on CMR, and decreased exercise tolerance when compared to patients without [25].

The principal aim of the PRIZE ET Sub-study is to identify additional novel, hitherto unknown functional genetic variants associated with microvascular angina, other than the rs9349379-G allele described above. For this reason, the study will run in parallel with the main PRIZE trial by preferential enrolment of the patients who are not selected after genetic screening for the rs9349379-G allele. Patient samples obtained in this parallel study will be genotyped using the UK Biobank Axiom^TM^ DNA Microarray. Briefly, the process involves extraction of DNA from whole blood, which is then denatured and fragmented, flourescentally labelled, and added to the array – a laborotary plate embedded with hundreds of thousands of DNA ‘probes’ (specific oligonucleotide sequences complementary to the genomic SNPs of interest). In the presence of a complementary DNA sequence, binding will occur by hybridization and scanning of the array for specific patterns of fluorescence can be used to identify genomic SNPs present in the patient's DNA [26]. In our study, analysis will be focused in the first instance, on SNPs located close to the gene encoding the ET_A_ receptor (EDNRA) with highly significant GWAS associations for ischemic heart disease, namely rs1878406 (Fig. 1) and rs6842241 (Fig. 2).

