**Fig. 2 f0010:**
[figure not shown]
Phenome wide associations for rs6842241 with disease traits identified from the UK Biobank[30]. Traits (blue dots) above the red dotted line have a p value for association of < 1 × e^-8^. Chronic Ischemic Heart Disease (labelled) shows the strongest association. (For interpretation of the references to colour in this figure legend, the reader is referred to the web version of this article.)

The rs1878406 SNP is located 8.5 kb upstream from the EDNRA gene on chromosome 4. The major rs1878406-C allele occurs with a frequency of 85% in Caucasian populations and is associated with cardiovascular risk, whereas the T allele is protective [27], [28]. The rs6842241 SNP is located 1.25 kb upstream from the EDNRA gene within the regulatory region. The risk allele (G) of rs6842241 has a frequency of 83% and is highly correlated (r^2^ > 0.8) with both rs1878406 and another SNP, rs6841581 located further upstream [29], which has been been identified in functional analysis as a possible epigenetic regulator of EDNRA gene expression [29].

We hypothesise that in a microvascular angina population, these SNPs related to the ET_A_ receptor, will result in greater ET_A_ receptor activation, reduced myocardial perfusion and more angina. Additionally, we wish to investigate whether higher ET_A_ receptor expression is associated with more severe disease, even amongst those without elevated circulating ET-1 levels.

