### Study procedures

2.2

Study blood handling will follow a standard operating procedure. Approximately 20 mL of venous blood will be withdrawn and collected. This will encompass a whole blood sample (4 mL) collected in PaxGene DNA tubes for DNA extraction and genotyping of ET_A_ SNPs, a second whole blood sample collected in PaxGene RNA tubes (2.5 mL) for quantification of ET_A_ mRNA and a 5 mL plasma sample for measurement of plasma endothelin related peptides. Blood will be centrifuged at 1500g for 20 mins at 4 °C. Plasma will be siphoned, aliquoted and stored at −80° ± 10°.

The PRIZE trial baseline clinical assessment includes patient interview, angina, quality of life and treatment satisfaction questionnaires, and Bruce protocol treadmill exercise testing (a full list of baseline assessments is provided in appendix B). These will be repeated at subsequent trial visits only if there have been significant changes in clinical status from initial screening otherwise results from these assessments will be used in the sub-study analyses.

SNP genotyping will be undertaken using the UK Biobank Axiom^TM^ Array. ET_A_ mRNA will be quantified in leucocytes and platelets within the samples using quantitative real-time polymerase chain reaction (qPCR). Big ET-1 and ET-1 will be measured by enzyme-linked immunosorbent (ELISA) immunoassay.

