## Statistical consideration

3

For sample size calculation, we considered a difference of 1.0 mL·g^−1^·min^−1^ for stress MBF on CMR clinically significant with a pooled standard deviation of 0.56 based on previous published data [14]. Additionally, based on pilot data from our laboratory, we have assumed a difference in circulating plasma ET-1 between patient groups of 0.4 pg/ml with a pooled standard deviation of 0.36 to be clinically meaningful. Power calculations for an independent samples *t*-test demonstrate that a sample size of 60 (estimated to give 51 patients with the risk associated rs1878406-C allele) will have > 80% power to detect significant differences in both stress MBF and in plasma ET-1 between patient genotypes with a level of significance of 0.05 for an alpha error (SPSS, IBM Corp., USA).

Normality of continuous variable distributions will be assessed using the one sample Kolmogorov-Smirnov Test. Continuous variables will be summarised as mean ± standard deviation if normally distributed and median (Inter-Quartile Range) if non-normally distributed. Appropriate paired difference tests will be used to compare continuous variables according to the normality of the distribution. The primary outcome measure will be the difference in the circulating concentrations of ET-1 related peptides and ET_A_ mRNA between observed genotypes. Secondary outcome measures will be exploratory, including differences in disease burden measured by questionnaires, exercise tolerance tests and perfusion CMR between various ET_A_ SNP genotypes. Clinical trials unit and data management support and storage will be via the use of OpenClinica.

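### The primary outcome bundles at least three biomarkers and two correlated SNPs with no lead test, and among its components only plasma ET-1 by rs1878406 was powered

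*Protocol article*

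**What the plan says.** All references are to the protocol article.

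- **Primary outcome** (section 3, Statistical consideration): "The primary outcome measure will be the difference in the circulating concentrations of ET-1 related peptides and ET_A_ mRNA between observed genotypes".
- **Peptides** (section 2.2, Study procedures): "Big ET-1 and ET-1 will be measured by enzyme-linked immunosorbent (ELISA) immunoassay". The plural in the primary outcome therefore means at least two.
- **mRNA** (section 2.2): ET_A "mRNA will be quantified in leucocytes and platelets within the samples using quantitative real-time polymerase chain reaction (qPCR").
- **SNPs** (section 1.3): the first analyses concern two variants near EDNRA, "namely rs1878406 (Fig. 1) and rs6842241 (Fig. 2"). Later in that section, the risk allele of rs6842241 "has a frequency of 83% and is highly correlated (r^2^ > 0.8) with both rs1878406 and another SNP, rs6841581".
- **Power** (section 3): a sample of 60, split by rs1878406, "will have > 80% power to detect significant differences in both stress MBF and in plasma ET-1 between patient genotypes".
- **Significance level** (section 3): the only one in the article belongs to that power calculation, which was made "with a level of significance of 0.05 for an alpha error".
- **Secondary outcomes** (section 3): "Secondary outcome measures will be exploratory"; perfusion CMR, and so stress MBF, is among them.

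**The concern.** A primary outcome should identify the test on which the study's main conclusion rests. This one identifies a family. Three biomarkers by two SNPs gives six comparisons, and nothing says which of them decides the result. A reader of the final report could not tell whether a significant result on one component was the planned primary finding or the best of six.

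The sample-size justification covers only one member of that family. Big ET-1 and ET_A mRNA have equal primary status but no target difference, standard deviation or power. ET_A mRNA is the measure closest to the hypothesis on receptor expression in section 1.3.

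The consequences reach beyond this sub-study. Section 5 says its findings could help to identify other patient groups likely to benefit from zibotentan, so a chance result on one component could be carried forward as a lead.

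**Working it through.** **Step 1. Reproduce the stated power.** Inputs from section 3: ET-1 difference 0.4 pg/ml, SD 0.36; stress MBF difference 1.0, SD 0.56; 60 patients, 51 in one group, so 60 − 51 = 9 in the other. Sidedness is not stated; two-sided is assumed. The split is taken as the plan gives it.

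Noncentrality = (difference / SD) / √(1/n₁ + 1/n₂), with 58 degrees of freedom.

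- √(1/51 + 1/9) = 0.3615.
- ET-1: 0.4/0.36 = 1.111, and 1.111/0.3615 = 3.07. Critical t = 2.00. Power = **85.6%**.
- Stress MBF: 1.0/0.56 = 1.786, and 1.786/0.3615 = 4.94. Power = **99.8%**.

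Both exceed 80%, so the plan's figure is correct for a single test at 0.05.

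**Step 2. Count the comparisons in the primary outcome.** ET-1, Big ET-1 and ET_A mRNA make three biomarkers. With two SNPs, 3 × 2 = 6. The mRNA is counted once, because the article does not say that leucocyte and platelet results are separate endpoints.

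**Step 3. Chance of at least one false positive if any component counts.** Each test is taken as two-sided at 0.05 under the global null. Six independent tests would give 1 − 0.95⁶ = 26.5%, but these tests are not independent. The article gives r² > 0.8 between the SNPs, so the two statistics for one biomarker correlate at more than √0.8 = 0.894. The correlation between biomarkers is not given and is varied from 0 to 0.9. Simulation of correlated normal test statistics (1,000,000 draws per cell) gives:

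| SNP r² | Biomarker correlation 0 | 0.5 | 0.7 | 0.9 |
|---|---|---|---|---|
| 0.8 | 19.8% | 17.3% | 15.1% | 11.7% |
| 0.9 | 18.2% | 15.9% | 13.8% | 10.6% |
| 1.0 (in effect one SNP) | 14.3% | 12.5% | 10.9% | 8.4% |

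The range is about **8% to 20%**. Because r² is stated only as above 0.8, the first row is an upper limit for each biomarker correlation.

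**Step 4. What splitting alpha does to the ET-1 power** at the plan's 51 v 9, with the same noncentrality of 3.07:

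| ET-1 tested at | Critical t | Power |
|---|---|---|
| 0.05 (alone or first) | 2.00 | 85.6% |
| 0.05/3 = 0.0167 | 2.47 | 72.7% |
| 0.05/6 = 0.0083 | 2.73 | 63.4% |

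So the stated power above 80% holds if ET-1 by rs1878406 is tested alone or first in a fixed order. It is not assured if alpha is shared over three or six primary tests.

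**The case against.** The strongest reply is that this is a condensed article. Multiplicity rules, testing order and success criteria commonly sit in a full protocol or SAP, and neither is shown. That stands as far as it goes: the absence of a multiplicity rule is not the finding. The finding is that the article itself fixes the primary outcome as a bundle and attaches its sample-size claim to one component.

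Several stronger readings are tempting and should be resisted.

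- **That the plan tests each component at 0.05 and so has a known inflated error rate.** The level appears only in the power calculation, and no rule says that any one significant component is a success. The two SNPs are named as an initial focus, not expressly as one primary family. The inflation is conditional and can only be given as a range.
- **That there are four biomarkers, because mRNA is measured in leucocytes and platelets.** The article describes one RNA sample and does not say that the cell types are separate endpoints.
- **That the power statement misses the primary outcome.** Plasma ET-1 is a named component and its power is correct. The statement covers part of the outcome.
- **That powering stress MBF is a mistake because it is secondary.** Powering a secondary outcome is no error, and section 3 shows its status openly.
- **That sharing alpha costs little.** At the plan's own split it takes ET-1 below the stated power.

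It can also be said that choosing ET-1 because it was powered moves the primary test away from receptor expression. That is fair. Which biomarker leads is the investigators' scientific choice; what matters is that they make it in advance and that the power claim matches it.

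**Conclusion.** The point holds in a limited form. The primary outcome comprises at least three biomarkers compared at two correlated SNPs, with no lead biomarker or contrast. Among those components, the 0.05 level and the power above 80% apply only to plasma ET-1 by rs1878406.

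The false-positive chance of about 8-20% rests on three assumptions: any component significant at two-sided 0.05 would count as a positive primary result, both SNPs belong to the primary family, and the correlations lie in the ranges tabulated. It is not a property that the article states. The power figures, 85.6% for ET-1 as a single test and 72.7% at one third of alpha, rest on the plan's own difference, SD and 51 v 9 split, and on a two-sided test.

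This should be corrected before analysis. It does not make the design unsound.

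**What to change.** Before the genotype data are analysed:

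1. Name one primary test, or a fixed testing order led by it. Plasma ET-1 by rs1878406 is the natural candidate, since the study is sized on it and it keeps the stated power (about 86% at 51 v 9).
2. Test Big ET-1 and ET_A mRNA afterwards as key secondary outcomes, with Holm adjustment between them.
3. Treat rs6842241 as a proxy sensitivity analysis for rs1878406, given r² > 0.8, and not as a second chance at the primary result.
4. If the investigators prefer three co-primary biomarkers with Holm adjustment, restate the ET-1 power. At 51 v 9 it lies between about 73% (if ET-1 has to pass at 0.05/3) and about 86% (if the other two have already been rejected). If another biomarker is to lead, give its target difference, SD and power.

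Items 1 to 3 change wording only and need no extra patients or samples. The cost is that Big ET-1 and ET_A mRNA take secondary status or face a stricter threshold. Item 4 has a real price in power at the planned sample size.

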### Patient selection:

2.1

The PRIZE trial will invite up to 356 participants from 8 UK sites for genetic testing and eligibility for progression into the randomisation phase. In Cambridge, approximately 100 patients will be enrolled into the PRIZE study. Once the results of genotype analysis and other baseline screening tests are available, it is expected there will be 66 screen failures and these patients will be approached to continue in the PRIZE Endothelin (ET) sub-study rather than the main PRIZE study (Fig. 3). This will include genetic screen failures as well as those found to have exclusion criteria during clinical assessment. We anticipate most of these patients (n = 60) will re-consent for the sub-study.

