### Additional participant analyses

2.3

If valid consent for the sub-study procedures is available for participants recruited to PRIZE from sites outside of Cambridge, they are found to be eligible, and surplus stored frozen samples are available, these will be similarly analysed.

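### The primary outcome is a difference between genotype groups, and the one contrast sketched isolates about one or two minor homozygotes; a per-allele regression would suit the hypothesis better

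*Protocol article*

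**What the plan says.** Section 3 (Statistical consideration) of the protocol article sets the primary outcome as the difference in "circulating concentrations of ET-1 related peptides and ET_A_ mRNA between observed genotypes". The secondary outcomes, labelled exploratory, are differences in symptom burden, exercise tolerance and "perfusion CMR between various ET_A_ SNP genotypes". No genetic model (additive, dominant or recessive) is named, and the number of groups to be compared is not stated. The analysis paragraph refers only to paired difference tests chosen by normality, which does not settle the contrast, because genotype groups consist of different patients.

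The one concrete contrast is in the power calculation, an independent-samples t-test with "a sample size of 60 (estimated to give 51 patients with the risk associated rs1878406-C allele", which leaves 9 others. It assumes a "difference in circulating plasma ET-1 between patient groups of 0.4 pg/ml with a pooled standard deviation of 0.36".

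Section 1.3 gives the frequencies: "The major rs1878406-C allele occurs with a frequency of 85% in Caucasian populations", and "The risk allele (G) of rs6842241 has a frequency of 83"%. It calls C the risk allele and T protective. Section 2.1 expects 60 patients: "We anticipate most of these patients (n = 60) will re-consent for the sub-study". Section 2.3 allows for more: if consent, eligibility and "surplus stored frozen samples are available, these will be similarly analysed". It gives no number.

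**The concern.** A biallelic SNP gives three genotypes, and when one allele is common the third group is tiny. If the primary outcome is tested as a difference between genotype groups, the answer depends on how that group is handled. The split that section 3 describes, C allele against no C allele, puts only TT patients on one side, so the weakest available contrast is the one a literal reader would run. A three-group test spends a second degree of freedom on those same few patients and ignores the ordering CC, CT, TT that a risk-allele hypothesis implies. At stake is the power of the primary comparison, and whether the coding is fixed before the genotype counts are seen.

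**Working it through.** **Inputs.** N = 60 (sections 2.1 and 3). Minor-allele frequency q = 0.15 for rs1878406 and 0.17 for rs6842241 (section 1.3). ET-1 difference 0.4 pg/mL, SD 0.36; stress MBF difference 1.0, SD 0.56 (section 3). Assumptions not in the document: two-sided 5% test, Hardy-Weinberg proportions, normal outcomes.

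**The plan's own figure.** For a two-group t-test the noncentrality is (δ/σ)/√(1/n₁ + 1/n₂). With 51 against 9 for ET-1 this is 1.111/√(1/51 + 1/9) = 3.07 on 58 df, giving 85.6% power. For MBF the power is 99.8%. The stated figure of over 80% is reproduced for that split.

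**Where the split comes from.** 0.85 × 60 = 51 applies an allele frequency to patients. Expected C carriers are 60 × (1 − 0.15²) = 58.65, leaving 1.35.

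**Expected genotypes.** 60(1−q)², 120q(1−q), 60q²; the minor-homozygote count is binomial(60, q²).

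| SNP | Major hom. | Het. | Minor hom. | P(0) | P(≤1) | P(≥3) |
|---|---|---|---|---|---|---|
| rs1878406 | 43.35 | 15.30 | 1.35 | 25.5% | 60.8% | 15.3% |
| rs6842241 | 41.33 | 16.93 | 1.73 | 17.2% | 47.9% | 25.1% |

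**Fixed splits, ET-1 difference 0.4.** 59 against 1: noncentrality 1.10, power 19%. 58 against 2: noncentrality 1.54, power 33%. CC against any T, 43 against 17: noncentrality 3.88, power 97%.

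**Random genotypes (simulation, N = 60, rs1878406, ET-1).** The plan does not say whether 0.4 is a per-allele difference or the CC-to-TT difference (0.2 per allele), so both are shown. Samples with no TT count as non-significant for C carriers against TT. Ranges show the spread between simulation runs of different length.

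| True effect | Per-allele regression | Three-group ANOVA | CC v any T | C carriers v TT |
|---|---|---|---|---|
| 0.2 per allele | 56% | 47–49% | 52–53% | 17–18% |
| 0.4 per allele | 98% | 97% | 97–98% | 43–44% |
| One T gives the full 0.4 | 94% | 93% | 96% | 10% |
| Only TT differs, by 0.4 | 11–12% | 18–19% | 6–7% | 22–23% |

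For rs6842241 at 0.2 per allele the four powers are about 60%, 50–51%, 56% and 20%. For stress MBF at 0.5 per allele (rs1878406) they are 91%, 87%, 89% and 33%.

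**Influence of TT patients in the regression.** At expected counts the mean T-allele count is 0.30 and the sum of squares is 15.3. A TT patient's leverage is 1/60 + (2 − 0.30)²/15.3 = 0.21, against an average of 2/60 = 0.033, so about six times the average.

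**The case against.** The strongest reply is that the article prescribes none of the worst analyses. The wording about observed genotypes defines an outcome, not a test. A trend test or CC against T carriers would fit it, and a condensed article may leave the coding to the full protocol or SAP. This stands in part. A reader might infer that the analyst is forced into three-group testing, pairwise tests or dropping TT; the text does not say so. What remains is that the article does fix a between-genotype difference as primary, and that the only split it describes is, on its own allele frequencies, the TT-isolating one.

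Second, a reader might infer a large loss of power in general. The figures do not support that. At 0.4 pg/mL per allele, regression, ANOVA and CC against T carriers are all near 97–98%. Even at 0.2 per allele, regression gains only about 3 points over CC against T carriers for rs1878406 and about 4 for rs6842241.

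Third, a reader might think regression rescues the TT group. It does not: it uses those patients under an assumed linear dose effect. It loses to ANOVA if only TT differs, and is 1–2 points below CC against T carriers if one T allele gives the full effect. Section 1.3 names a risk allele but does not claim additivity. The leverage of TT patients is a real cost.

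Finally, one or two minor homozygotes is an expectation and not a bound. Three or more are quite possible, and samples under section 2.3 could add to them.

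**Conclusion.** The point holds in limited form. On the document's own frequencies and N = 60, a comparison that isolates the minor homozygotes is impossible in 17–26% of samples. For ET-1 and rs1878406 its power is about 17–18% (0.2 per allele) to 43–44% (0.4 per allele). If the effect is additive, a three-group test gives up about 7–9 points against a per-allele test at 0.2 per allele for rs1878406 (9–10 for rs6842241), and about 1 point at 0.4. The case for a per-allele model is that it keeps the primary outcome off these two contrasts and matches a hypothesis about a risk allele; any advantage over CC against T carriers is minor. The conclusion rests on Hardy-Weinberg proportions, a two-sided 5% test, normal outcomes, and 60 patients with no added samples.

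**What to change.** In section 3, replace the group difference with wording such as: each outcome is analysed by linear regression on the number of risk alleles (0, 1, 2), on the log scale for skewed biomarkers; the result is the per-allele difference (a ratio on the log scale) with its 95% CI and a 1-df test; means by genotype are descriptive; CC against T carriers is a sensitivity analysis (and the corresponding grouping for rs6842241); the influence of minor homozygotes is checked by refitting without them. Apply the same model to the exploratory outcomes, and restate the power calculation on that model and on expected genotype counts, saying whether 0.4 pg/mL is per allele or CC to TT.

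The cost is a few sentences, with no new patients or measurements. The price is the additivity assumption: TT remains untestable on its own, a little power is lost if the T effect is dominant, and more is lost against ANOVA if the effect is confined to TT.
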